#### Secondary

##### The NIHSS

The NIHSS is a standardized stroke severity scale used to describe neurological deficits in stroke patients. The NIHSS comprises tests of 11 items, including the level of consciousness, selected cranial nerves, motor function, sensory function, cerebellar function, language, and inattention (neglect) et al. Total scores range from 0 to 42, with scores above 25 indicating very severe neurological impairment, scores of 5–24 suggesting moderately severe to severe impairment, and scores below 5 indicating mild impairment [15].

Each patient will be scored by a trained, certified investigator at the time of initial stroke evaluation (baseline) and at 4, 12 and 24 weeks after treatment.

##### The mRS

The mRS is another commonly used scale that measures disability or dependence in activities of daily living in stroke victims [16]. Consenting patients with stroke in this trial will have the mRS performed by the investigators at baseline and at 4, 12 and 24 weeks.

#### Follow-up

Assessments will be conducted at baseline and at weeks 4, 12 and 24 of follow-up. The follow-up assessment is designed to evaluate the long-term effect of acupuncture treatment.

### Quality control

The staff will be specially trained to treat stroke patients; they will take part in special education programs to improve their knowledge of stroke. They will be trained to know the inclusion and exclusion criteria, and all the occupational therapists will master the acupuncture methods used in this trial.

Patients will be allocated to different groups using a random number table to avoid selection bias. Blinding will be used both for the evaluators and the patients to avoid measurement bias and the influence of psychological factors on the therapy effect. All statistical analysis will be conducted by the statistician, who will be blinded to the grouping and analysis procedure.

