**Method:**

Three hundred and twenty eight subjects with acute cerebral apoplexy will be recruited. The patients will be randomized into two different groups: the intervention group will receive acupuncture treatment together with Western standard treatment for 2 weeks plus the secondary prevention treatment for 22 weeks; the control group will receive only the Western standard treatment for 2 weeks and the secondary prevention treatment for 22 weeks. The primary outcome measures are Barthel Index and the Stroke-Specific Quality Of Life. The secondary outcome measures are the National Institutes of Health Stroke Scale and Modified Rankin Scale. All assessments will be conducted at the baseline and at weeks 4, 12 and 24 of follow-up.

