## Methods/design

### Study design

The study is a parallel multi-center randomized controlled trial. It will compare the combination of acupuncture and Western medicine treatments with standard Western stroke treatment given alone during the acute phase (24 weeks) after stroke. The Barthel Index (BI) and Stroke-Specific Quality Of Life (SS-QOL) will be assessed as primary outcome measures, and the secondary outcome measures are the National Institutes of Health Stroke Scale (NIHSS) and modified Rankin Scale (mRS). All assessments will be conducted at baseline and at weeks 4, 12 and 24 of follow-up. The study design is detailed in Figure 1.

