#### Intervention group

Seven main acupoints will be stimulated: Baihui (Du-20), Quchi (LI-11), Shousanli (LI-10), Hegu (LI-4), Zusanli (ST-36), Yanglingquan (GB-34), and Sanyinjiao (SP-6). Acupoints association will be used according to the theory of Chinese medicine and the unique symptoms of the patients. The following additional acupoints are commonly used: Jianyu (LI-15), Huantiao (GB-10), Qiuxu (GB40), twelve well-jing points, Jinjin (EX-HN 12), Yuye (EX-HN 13), Yamen (DU-15), Lianquan (RN 23), Tianshu (ST-25), Fenglong (ST-40), and limb spasm assists with fire needles.

The acupoints will be stimulated by filiform stainless-steel needles (0.30 mm diameter, 40 mm length). Patients in the acute stroke stage will be manually stimulated to elicit needle sensation (de qi) at the main acupoints detailed above, with a needling depth of 30 mm. The needles will remain for 30 minutes per treatment, and the treatments are given five times per week. At the same time, Jinjin (EX-HN 12), Yuye (EX-HN 13), Sishencong (EX-HN 1) and the twelve jing well points will be stimulated by quick insertion of the tri-ensiform needles to induce bleeding. The stimulation will last for two weeks. Stimulation of Jianyu (LI-15), Huantiao (GB-10), Qiuxu (GB40), Yamen (DU-15), Lianquan (RN 23), Tianshu (ST-25) and Fenglong (ST-40) will be performed according to the specific syndrome of each patient. For instance, Jianyu (LI-15) and Huantiao (GB-10) will be selected for hemiplegic paralysis; Yamen (DU-15) and Lianquan (RN 23) for aphasia; and Tianshu (ST-25) and Fenglong (ST-40) for constipation.

Western medicine standard therapy, such as inhibition of platelet aggregation, control of blood pressure, routine physiotherapy, occupational therapy, glucose control, dyslipidemia control, and dehydration treatment if necessary, will be given for 2 weeks. The secondary prevention treatments, such as blood pressure control, inhibition of platelet aggregation, glucose control, and dyslipidemia control, will be given for 22 weeks.

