#### Control group

The patients will receive the standard therapy for 2 weeks and the secondary prevention treatment for 22 weeks as mentioned above.

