#### Primary

##### The BI

The BI is a scale that measures ten basic aspects of activity related to self-care and mobility [13]. For the Chinese version, the BI is translated into Chinese, and the ten items are: feeding, bathing, grooming, dressing, continence of bowels and bladder, transferring to and from a toilet, moving from wheelchair to bed and return, walking on level surface for 45 meters, and going up and down stairs. The sum of the scores for the individual items forms the total score. The normal score is 100, and lower scores indicate greater dependency. If a person manages about 50% of the items independently, their score would fall in middle.

The BI will be assessed by the investigators at baseline and at 4, 12 and 24 weeks after the stroke. The total BI scores will be recorded and classified into three groups: independent (BI score ≥ 60), with help (BI score 40–60), and dependent (≤ 40).

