##### The SS-QOL

The SS-QOL is a patient-reported outcome measure intended to provide an assessment of health-related quality of life, specific to patients with stroke [14]. The SS-QOL questionnaire consists of 49 items in the 12 domains of energy, family roles, language, mobility, mood, personality, self-care, social roles, thinking, upper extremity function, vision, and work/productivity. Scoring of the SS-QOL is rated on a 5-point Likert scale. Response options are scored as 5 (“no help needed/no trouble at all/strongly disagree”), 4 (“a little help/a little trouble/moderately disagree”), 3 (“some help/some trouble/neither agree nor disagree”), 2 (“a lot of help/a lot of trouble/moderately agree”), and 1 (“total help/could not do it at all/strongly agree”). The domains are scored separately, and a total score is also calculated, with higher scores indicating better function.

An SS-QOL version translated to Chinese will be provided to the patients at baseline and at 4, 12 and 24 weeks. The test-retest reliability, internal consistency, construct, and convergent validity of the SS-QOL in patients with stroke will be ascertained by the investigators.

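### Patients are said to be blinded, but the arms described make this impossible, so the patient-reported primary outcome (SS-QOL) lacks the protection claimed for it

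*Protocol article*

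**What the plan says.** Quality control makes a positive statement with a stated purpose: "Blinding will be used both for the evaluators and the patients to avoid measurement bias and the influence of psychological factors". It adds that the statistician will be blinded.

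The control condition is described consistently. The abstract's Method says that "the control group will receive only the Western standard treatment for 2 weeks and the secondary prevention treatment for 22 weeks". The Control group section says: "The patients will receive the standard therapy for 2 weeks and the secondary prevention treatment for 22 weeks as mentioned above". Study design describes an add-on comparison: "It will compare the combination of acupuncture and Western medicine treatments with standard Western stroke treatment given alone". Interventions agrees. No section describes a sham or placebo procedure; the word sham appears only in the Discussion, about a cited meta-analysis.

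On the other arm, the Intervention group section says: "Patients in the acute stroke stage will be manually stimulated to elicit needle sensation (de qi) at the main acupoints detailed above". Needles stay in for 30 minutes, five times a week. Other points are pricked to induce bleeding, and the stimulation lasts two weeks.

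The two primary outcomes are the Barthel Index (BI) and the SS-QOL. On the latter: "The SS-QOL is a patient-reported outcome measure". It is given to patients at baseline and at weeks 4, 12 and 24. For the other: "The BI will be assessed by the investigators at baseline", and again at the three later visits. The NIHSS and mRS are likewise scored by investigators.

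**The concern.** The article claims a safeguard that its own design excludes. A patient who has been needled and pricked over two weeks knows it, and so does a patient who has not. Informed consent adds to this, since patients are told about the study process beforehand.

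This matters most for the SS-QOL, because the person who answers it is the person said to be blinded. If patients expect acupuncture to help, or respond to the additional attention, their answers can shift without any effect of the needles. The article says that blinding prevents exactly this influence. A reader or meta-analyst who takes the statement at face value would place more trust in an SS-QOL difference than the design supports. The Discussion also names change in quality of life as the primary endpoint, so the affected outcome is central to the conclusion.

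**Working it through.** **Step 1: what each patient experiences**

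| | Intervention arm | Control arm |
|---|---|---|
| Standard treatment, 2 weeks | yes | yes |
| Secondary prevention, 22 weeks | yes | yes |
| Needling to elicit sensation, 5 times a week | yes (5 × 2 = 10 sessions over two weeks) | none |
| Pricking to induce bleeding | yes, within the two weeks | none |
| Sham procedure | not applicable | none described |

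The arms differ by a procedure that patients feel and see. Patient blinding is not achievable under this description. Figure 1 is not available, but the abstract, Study design, Interventions and Control group sections all define the control arm in the same way.

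**Step 2: which outcomes depend on patient blinding**

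The SS-QOL is answered by the patient, so it is unblinded. BI, NIHSS and mRS are scored by someone else, and Quality control plans blinded evaluators. These three can be protected in principle, although a patient may disclose the allocation.

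**Step 3: an illustration of size**

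There is no stated figure to reproduce. The total of 328 is the only design figure given; no effect size, SD, power or dropout accompanies it.

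Inputs from the article: 328 patients (Interventions); two-sided 0.05 (Statistical analysis).

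Assumptions: equal allocation, so 328 / 2 = 164 per arm (the ratio is not stated); no dropout; no true effect; a constant reporting bias of b SD in favour of acupuncture; a simple comparison of two means at one visit. The values of b are assumed, as the article gives none.

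- Standard error of the difference: sqrt(2/164) = 0.110 SD.
- Smallest significant difference: 1.96 × 0.110 = 0.22 SD.
- Chance of P < 0.05: P(Z > 1.96 − b/SE) + P(Z < −1.96 − b/SE).

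| Bias b (SD) | b/SE | Chance of P < 0.05, 164 per arm | Same, assumed 20% loss (131 per arm) |
|---|---|---|---|
| 0 | 0 | 5% | 5% |
| 0.1 | 0.91 | 14.8% | about 13% |
| 0.2 | 1.81 | 44.1% | about 37% |
| 0.3 | 2.72 | 77.5% | about 68% |

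For the last column, 328 × 0.8 / 2 = 131 per arm and SE = sqrt(2/131) = 0.124 SD.

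**The case against.** The strongest defence is that an add-on trial without sham is a legitimate pragmatic design. It validly estimates what happens when acupuncture is added to usual care, non-specific effects included. Study design says plainly that this is the comparison, and the abstract aims at integrated treatment strategies. This stands: no sham arm is needed, and the defect lies in the blinding statement and in how an SS-QOL difference would be read.

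It can also be said that the illustration is generic. It would apply to any open-label trial of this size, the bias is assumed, and a bias arising from two weeks of needling may have faded by week 12 or 24. That also stands. The figures show sensitivity to bias and do not estimate the bias in this trial.

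Two stronger readings are tempting, and the document supports neither.

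- A reader might infer that BI, NIHSS and mRS are rated unblinded, because the outcome sections say investigators where Quality control says evaluators. Nothing shows that these are different people. Treatment is attributed to occupational therapists, and the one evaluation attributed to an acupuncturist (Randomization) precedes allocation. The investigators may well be the blinded evaluators. What remains is an inconsistency of terms, worth clearing up because BI is the only primary outcome that blinding can protect.
- A reader might infer that BI should be placed ahead of SS-QOL in the primary analysis. The defect does not require this. The abstract and Study design give the two equal standing, and the Discussion puts quality of life at the centre, so demoting SS-QOL would be a debatable preference.

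**Conclusion.** The patient-blinding statement in Quality control is wrong as written and has to be corrected. This rests on the article's own text and needs no assumption. It is not a detail left to a fuller document, because the article asserts a property that its arms exclude.

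The consequence is confined to interpretation of the SS-QOL: a difference there would combine any effect of needling with expectation and extra contact. Under the assumptions listed above, a modest bias of 0.2 SD alone would give a significant result in about 44% of trials (about 37% with 20% loss). The range is 15% to 78% for biases of 0.1 to 0.3 SD.

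The point does not show that evaluators are unblinded, that the BI is compromised, or that the add-on comparison is invalid.

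**What to change.** - **Quality control:** delete the claim that patients are blinded, and with it the claim that blinding removes psychological influence on the treatment effect. Describe the trial as open-label to patients, with blinded outcome evaluators and a blinded statistician.
- **The BI, The NIHSS and The mRS:** use one term throughout. State that these scales are scored by the blinded evaluators already planned, who take no part in treatment and ask patients not to reveal their group.
- **Abstract (Discussion) and main Discussion:** state that the trial estimates the effect of adding the acupuncture package (needling together with contact and expectation) to standard care, and that SS-QOL is an unblinded outcome.

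No change to the arms, the sample size or the order of the primary outcomes is needed. The cost is mostly wording. If some scoring investigators also treat patients, the scoring would have to pass to the evaluators. The real price is a weaker claim for the SS-QOL, which the design could not have supported in the stronger form.

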### Statistical analysis

The statistical analysis will be performed by the Epidemiological Research Center of the Third Affiliated Hospital of Beijing University.

The quantitative data are presented as mean ± standard deviation and will be analyzed using analysis of variance when normally distributed. Non-parametric data will be analyzed using the Wilcoxon test with repeated measures. Enumeration data are presented as frequencies or ratios. If the outcome variables are two-way 2×2 contingency tables, chi-square tests or Fisher exact probability tests will be performed. If they are one-way 2×4 ordered data, Ridit analyses will be performed.

Statistical analyses will be conducted using SPSS version 13.0 (SPSS, Chicago, IL, USA). The P-value cut-off for statistical significance is defined as *P* < 0.05, and all statistical tests are two-tailed.

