Recovery of function after stroke is a long steady process that continues for several weeks or even months before reaching a stable phase. The effects of acupuncture occur within the same time frame. Several previous studies did not show any beneficial effect of acupuncture, and this may in part be explained by an assessment of efficacy too soon after acupuncture treatment (in most cases 2–3 weeks after stroke) [22,23]. An assessment or reassessment at a minimum of 4 weeks, and ideally at least 3 to 6 months after the completion of treatment is essential. We followed the time course of the normal process of stroke recovery in designing our study protocol. Thus, we will assess efficacy at baseline and at 4, 12 and 24 weeks after acupuncture intervention.

The primary endpoint for this study is the change in the quality of life in the intervention and control groups, from baseline to 4, 12 and 24 weeks post-therapy. Neurological deficits, disability, and dependence in activities of daily living will be evaluated by NIHSS and mRS as the secondary endpoints.

Many acupuncturists consider the main effect of acupuncture on the human body after stroke to be the rehabilitation of motor function, whereas few have considered the patients’ life quality, which includes factors such as dependence in activities of daily living, feeding, dressing, and continence of bowels and bladder. To address this, we will use the BI and SS-QOL questionnaires to measure the quality of life as the primary outcomes.

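### For normally distributed primary scores the plan names only analysis of variance and does not say how each patient's repeated visits enter it; a baseline-adjusted mixed model would settle this

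*Protocol article*

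**What the plan says.** The Study design section sets the schedule: "All assessments will be conducted at baseline and at weeks 4, 12 and 24 of follow-up". The outcome sections repeat it for each primary measure: "The BI will be assessed by the investigators at baseline and at 4, 12 and 24 weeks after the stroke" and "An SS-QOL version translated to Chinese will be provided to the patients at baseline and at 4, 12 and 24 weeks". Each patient therefore contributes up to four values per score, three of them after baseline. (The time origin is worded differently from place to place. That is a separate matter and does not change the number of visits.)

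The Discussion defines the endpoint: "The primary endpoint for this study is the change in the quality of life in the intervention and control groups". It measures that change over all three follow-up visits, "from baseline to 4, 12 and 24 weeks post-therapy", and then names BI and SS-QOL as the measures of it.

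The Statistical analysis section has one sentence for each kind of quantitative data. For normal data: "The quantitative data are presented as mean ± standard deviation and will be analyzed using analysis of variance when normally distributed". For the rest: "Non-parametric data will be analyzed using the Wilcoxon test with repeated measures". The level is common to both: "The P-value cut-off for statistical significance is defined as *P* < 0.05, and all statistical tests are two-tailed". The section does not give the factors in the analysis of variance, does not mention a patient term, and does not say whether the three visits are tested together or one at a time.

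**The concern.** Patients are randomised, but scores come per patient and visit, and scores from one patient are correlated. The authors evidently had this in mind, because the non-parametric sentence refers to repeated measures. The sentence beside it, for the same scores at the same visits, does not. Taken at face value, a normality check would then decide not only which test is used but also whether the correlation is allowed for.

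What is at stake depends on how the analysis of variance is run:

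- **All visits in one analysis with a single residual.** The arm effect is tested against too small an error, and the arm-by-visit effect against too large an error.
- **One analysis per visit.** Each test is valid, but a patient who misses a visit is lost at that visit, and no test asks whether the arms diverge over time.
- **Classical repeated-measures analysis of variance.** The error terms are right, but a patient who misses any visit is dropped entirely.

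**Working it through.** **Inputs from the article.** Total sample 328; two arms; three post-baseline visits; two-sided level 0.05.

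**Assumptions, not in the article.** 1:1 allocation (164 per arm); no missing visits; the same correlation rho between any two visits, baseline included. The article gives no error rate for this analysis beyond the nominal 5%, so there is no further figure to reproduce.

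**Step 1: correlation of the change scores.** Take a raw-score variance of 1.
- Variance of a change score: 1 + 1 − 2·rho = 2(1 − rho).
- Covariance of two change scores from the same patient: rho − rho − rho + 1 = 1 − rho.
- Correlation: (1 − rho) / [2(1 − rho)] = 0.5, whatever rho is.

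**Step 2: arm effect if visits are pooled without a patient term.** With T visits and correlation r between the analysed scores, the true variance of the arm difference is 1 + (T − 1)r times what the plain analysis assumes. The false-positive rate is 2·[1 − Φ(1.960 / √(1 + (T − 1)r))].
- At r = 0 this returns the nominal 5%.
- For change scores, T = 3 and r = 0.5: inflation 1 + 2 × 0.5 = 2; 1.960 / √2 = 1.386; rate **16.6%**.

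**Step 3: arm-by-visit effect in the same pooled analysis.** The true variance is (1 − r) times what is assumed. The residual degrees of freedom are 328 × 3 − 6 = 978, and the 5% critical F on 2 and 978 degrees of freedom is about 3.005. The rate is P(χ² on 2 df > 2 × 3.005 / (1 − r)). At r = 0.5 the threshold is 12.02 and the rate is **about 0.2%**. Where a correct test of this effect would have 80% power, the plain test would have about 42%.

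**Step 4: range.** If raw scores were analysed, or if the correlation is not equal across visits, r need not be 0.5. With three visits:

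| r | Arm effect, nominal 5% | Arm-by-visit, nominal 5% | Plain arm-by-visit power where the correct test has 80% |
|---|---|---|---|
| 0.3 | 12.1% | 1.4% | 64% |
| 0.5 | 16.6% | 0.2% | 42% |
| 0.7 | 20.6% | below 0.1% | 11% |

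**Step 5: simulation.** This used 10,000 replicates with 164 per arm, three visits and r = 0.5.
- Plain pooled analysis: arm 17.2%, arm-by-visit 0.4%.
- With a patient stratum: arm 5.0%, arm-by-visit 4.9%.
- Analysis of variance at one visit only: 5.2%.

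The error rates therefore go wrong only under pooling without a patient term. A patient stratum, or testing one visit at a time, restores the level.

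**The case against.** The strongest reply is that the harmful analysis is nowhere in the document. No sentence specifies a two-way arm-by-visit analysis, a pooled residual, or patient-visits as the unit of analysis. The same words fit an analysis of the change score at each visit, which the endpoint's wording readily suggests, and they also fit a repeated-measures analysis of variance named in short form. Both keep the 5% level when the data are complete. A journal article also commonly leaves factors, error strata and covariance structure to a fuller document.

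Most of this stands. A reader might infer that the plan commits to a pooled analysis and so carries a false-positive rate somewhere between 12% and 27%. The documents do not support that. No patient term is named, but none is excluded. The upper part of that range also comes from entering baseline as a fourth outcome visit, which is not an analysis of change. Nor can the long-term aim be equated with the arm-by-visit test: a between-arm comparison at week 24 also addresses it.

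Two things survive. First, this is not simple silence: repeated measures are addressed in one of two adjacent sentences about the same data and left out of the other. Second, even the valid readings handle missed visits poorly, so a better method than the one named is available at almost no cost.

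**Conclusion.** The point holds as an under-specified and improvable primary analysis, not as a demonstrated error-rate failure. For normally distributed BI and SS-QOL scores, the Statistical analysis section does not say how three correlated follow-up values per patient are handled, although its non-parametric sentence does refer to repeated measures.

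The size is conditional. Pooling change scores without a patient term would give an arm-effect error of about 16.6% and an arm-by-visit error of about 0.2%, both against 5%, assuming equal correlation including baseline, 1:1 allocation and complete data. For other between-visit correlations from 0.3 to 0.7, the arm-effect error would be 12.1% to 20.6%. Visit-by-visit analysis has no error-rate problem at any single visit. Its costs are the loss of patients who miss that visit and the absence of any test of divergence. The article gives no rate of missed visits, so that loss cannot be put in numbers.

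**What to change.** In the Statistical analysis section, replace analysis of variance for BI and SS-QOL with a mixed model for repeated measures:

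- **Outcome:** the score at weeks 4, 12 and 24.
- **Fixed effects:** arm, visit, arm-by-visit, baseline score and baseline-by-visit. With baseline in the model, the between-arm difference in the follow-up score is also the baseline-adjusted difference in change, so the stated endpoint is kept.
- **Within-patient covariance:** unstructured.
- **Report:** the between-arm difference with its confidence interval at each visit, and the arm-by-visit test as the assessment of divergence.

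The model allows for the within-patient correlation and keeps a patient who has a baseline value and at least one follow-up value.

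**Cost.** The change is to the analysis wording. It needs no additional patients, visits or measurements beyond those already scheduled. There is a little more analysis work, and the statistician should confirm that the software named in the plan fits this model. The model relies on data being missing at random given the observed scores. That assumption should be stated, because it may fail if patients miss visits for reasons that their recorded scores do not capture.

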## Background

With the rapid economic development in China, the Chinese healthcare system has seen significant improvements. However, tough challenges remain in the treatment of stroke, the leading cause of death and disability in China [1]. Although stroke is a global epidemic, about 85% of all stroke deaths are registered in low- and middle-income countries, and patients in these countries also account for 87% of total stroke-related losses in terms of disability-adjusted life years [2]. For example, in China, stroke morbidity is 89.6–314 out of every 100,000 males and 76.7–212.2 out of every 100,000 females. The mortality from stroke in urban areas is 127.96 out of every 100,000 people, and in rural areas 115.2 out of every 100,000 people [3].

Poor control of vascular risk factors and limited access to acute and primary care are the most common reasons for the high mortality and rate of disability after stroke. In addition, secondary prevention-an important possible approach in the treatment of stroke-is also largely lacking in low- and middle-income countries [4].

Despite the availability of effective therapies, optimal management of stroke remains problematic. Current therapeutic strategies focus on restoring blood flow in ischemic strokes, and on controlling bleeding in hemorrhagic strokes. These approaches are not effective for long-term stroke recovery or for enhancing the quality of life of patients. For example, thrombolytic therapy carries the risk of hemorrhage and is limited to the first three hours after the stroke [5-7].

Acupuncture has been practiced in China for more than 3,000 years [8], and is traditionally considered as a treatment for various ailments associated with stroke. Recently, there have been many reports of its benefits in the treatment of stroke [9-11]. However, the effect size of these clinical studies was underestimated because of methodological flaws, including inadequate statistical analysis, a failure to describe differences in baseline stroke severity, and an inadequate assessment period [11,12]. Thus, acupuncture may be more effective in assisting stroke recovery than has generally been reported, especially when the stroke is moderately severe.

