### Interventions

A total of 328 patients in the acute stage of cerebral apoplexy will be recruited. The patients are randomly divided into two different groups: 1) the intervention group and 2) the control group. The intervention group will receive acupuncture treatment in addition to the Western medicine standard treatment for 2 weeks and the secondary prevention treatment for 22 weeks, and the control group will receive standard Western-medicine therapy for 2 weeks and the secondary prevention treatment for 22 weeks. Both groups will be evaluated at baseline and at 4, 12 and 24 weeks of treatment.

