### Outcome measures

#### Participant demographics and general status

Demographic information such as sex, age, marital status, educational background, indicators of social economic status (e.g. household income) and time from attack will be extracted from baseline questionnaires. Vital signs (respiration rate, pulse, blood pressure and temperature) will be measured by nurses.

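### The stated analysis of the primary scores has no baseline covariate and switches test on normality; adjusting for baseline would be more precise and would correct chance imbalance in severity

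*Protocol article*

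**What the plan says.** The Statistical analysis section states that quantitative data "will be analyzed using analysis of variance when normally distributed"; data that are not normal go to a Wilcoxon procedure for repeated measures. It does not assign tests to outcomes by name, but the BI and SS-QOL totals are quantitative scores, so the rule covers them. Neither that section nor any other names a baseline score, a severity measure or the hospital as a model term. The Randomization section mentions no stratification.

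The abstract and Study design name the BI and SS-QOL themselves as primary outcomes. The Discussion puts it differently: "The primary endpoint for this study is the change in the quality of life in the intervention and control groups", measured from baseline to weeks 4, 12 and 24.

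The material for adjustment is collected. All four scales are scored at baseline, and "time from attack will be extracted from baseline questionnaires". Entry admits NIHSS 4 to 21 and onset up to 14 days earlier. Among the faults of earlier trials, the Background lists "a failure to describe differences in baseline stroke severity", and the Discussion holds that the effect of acupuncture varies with stroke severity.

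**The concern.** Patients enter over a wide range of severity and at different times after onset, so the baseline score and NIHSS can be expected to predict later function. An analysis with no baseline covariate leaves that explained variation in the error term. Taking the change score instead is not equivalent to adjustment: it subtracts the whole baseline value whatever the correlation, which adds noise when the correlation is low and over-corrects any baseline imbalance.

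Two things are at stake. One is power at a fixed 328 patients. The other is how the result reads if the arms differ by chance in baseline severity: the stated analysis has no means of correcting for that.

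The rule for choosing the test is a further difficulty. Analysis of variance compares means and a Wilcoxon test compares ranks. The BI is bounded at 100, so skew is likely as patients recover. Under the stated rule, the type of comparison could differ between scales or visits according to the distribution observed.

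**Working it through.** **No planned figure to reproduce.** The article gives the sample size but no effect size, SD, power or dropout rate. What follows is an illustration.

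**Inputs from the article**
- Sample size: "A total of 328 patients in the acute stage of cerebral apoplexy will be recruited" (Interventions).
- Two arms: "The patients are randomly divided into two different groups" (Interventions).
- Test level: "The P-value cut-off for statistical significance is defined as" P < 0.05, and "all statistical tests are two-tailed" (Statistical analysis).

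**Assumptions, not in the article**
- Allocation 1:1, so 164 per arm.
- Equal SD at baseline and follow-up, set to 1.
- Baseline-outcome correlation r of 0.4, 0.5 or 0.6.
- A true difference of 0.31 SD. This is roughly what the unadjusted follow-up score detects with 80% power: (1.96 + 0.842) × √(2/164) = 2.802 × 0.1104 = 0.309.

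**Power.** The standard error is 0.1104 × √factor, and power = Φ(0.31 / (0.1104 × √factor) − 1.96). The variance factor is 1 for the follow-up score, 2(1 − r) for change, and 1 − r² with baseline adjustment (ANCOVA).

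| r | Factor: change | Factor: adjusted | Power: follow-up score | Power: change | Power: adjusted |
|---|---|---|---|---|---|
| 0.4 | 1.20 | 0.84 | 80% | 73% | 86% |
| 0.5 | 1.00 | 0.75 | 80% | 80% | 90% |
| 0.6 | 0.80 | 0.64 | 80% | 88% | 94% |

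**Equivalent sample size.** This is the number of patients that the unadjusted analysis needs to match adjustment with 328.
- On the follow-up score, 328/(1 − r²): 328/0.84 = 390, 328/0.75 = 437, 328/0.64 = 512.
- On change, 328 × 2(1 − r)/(1 − r²) = 656/(1 + r): 656/1.4 = 469, 656/1.5 = 437, 656/1.6 = 410.

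The two series move in opposite directions as r rises, so the gain depends on which quantity the trial analyses. The direction does not: 1/(1 − r²) and 2/(1 + r) both exceed 1 for every r strictly between 0 and 1.

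**Chance imbalance.** With simple randomization the standard error of a baseline difference is 0.1104 SD. A difference beyond 0.2 SD in either direction has probability 2 × (1 − Φ(0.2/0.1104)) = 7.0%. Suppose the baseline score happens to differ by 1.96 standard errors. Under no treatment effect, the follow-up test statistic then has mean 1.96r and variance 1 − r². For r = 0.5 the mean is 0.98 and the SD 0.866, so the chance of significance is 1 − Φ(0.98/0.866) plus a negligible lower tail = 12.9%. For a change score the correlation with baseline is −√((1 − r)/2), which is −0.5 at r = 0.5 and gives the same 12.9%. Over r = 0.3/0.5/0.7 the conditional error is 7.9%/12.9%/20.5% for the follow-up score and 16.0%/12.9%/9.8% for change. Averaged over all randomizations it is 5%.

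**Hospital.** If hospital explained an assumed 2% to 10% of the variance, adjusting for it would raise power from 80% to about 81% to 84%.

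**The case against.** The strongest reply is that a journal article condenses the plan, that model covariates normally belong in a statistical analysis plan not shown here, and that silence on covariates is not a decision to leave them out. That would answer a complaint about missing detail. It has less force here because the article does fix the method: it names the tests and makes the choice depend on normality. A plan with one adjusted model per score would have to replace that sentence.

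Other parts of the defence stand, and they rule out stronger readings.
- A reader might infer that baseline is ignored altogether. The Discussion's endpoint is a change, so baseline enters by subtraction. A repeated-measures analysis of variance, with baseline as one of the times, is also compatible with the wording. What is missing is baseline as a covariate.
- A reader might infer that the comparison is biased or invalid. Randomization keeps it unbiased, and overall type I error is 5%. The conditional error rates above apply only to a trial that happens to be imbalanced.
- A reader might infer that the article contradicts its own Background. That passage faults a failure to describe severity differences. This trial records severity at baseline and so can describe it. The passage lends weight to adjustment but does not require it.
- A reader might treat the 390/437/512 series as the gain in all cases. It applies to the follow-up score only.
- The power figures are for comparisons of means. If the BI proves skewed and goes to the Wilcoxon test, they do not describe that analysis.
- The article speaks of normally distributed data but sets no formal test or threshold, and the effect of the switch has not been sized.

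**Conclusion.** The point holds as one of efficiency and of protection against chance imbalance, not of validity. Under either reading of the endpoint, the stated method is less precise than adjustment for the baseline score. At the assumed correlations the gain is about 6 to 14 percentage points of power over the follow-up score (86 − 80 to 94 − 80) and 13 to 6 points over change (86 − 73 to 94 − 88). These sizes rest on 1:1 allocation, equal SDs, a 0.31 SD difference and r between 0.4 and 0.6, none of which the article gives. The direction needs only a positive correlation below 1. The case rests on the baseline score and severity; the hospital term adds little. The switch between mean and rank comparisons is a secondary defect, because it leaves the effect being tested to the observed data. The change is worth making because the covariates are already collected.

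**What to change.** For the BI and SS-QOL, replace the normality-dependent sentence with one pre-specified model per score, used whatever the distribution looks like: either ANCOVA, or a mixed model over weeks 4, 12 and 24 with arm, visit and arm-by-visit terms. Include as covariates the baseline score of the same scale and baseline NIHSS. Days from stroke and hospital are optional, with a small gain expected. State that the arm difference is reported with its 95% confidence interval. With the baseline score as a covariate, follow-up score and change give the same estimated arm difference, so the two descriptions of the endpoint no longer lead to different results. Because of the BI ceiling, add a rank-based or ordinal analysis of the BI with the same covariates as a sensitivity analysis. Which visit is primary is a separate matter that this change does not have to settle.

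The cost is revised wording and slightly more programming, with no new data and no extra patients.
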